#### Intervention period

Treatment group: Participants will take usual treatment and SQXT formula granules, which is composed of Shengshaishen (Dried fresh Ginseng), Zhihuangqi (Astragalus membranaceus), Shanyao (Common Yam Rhizome), Shengdihuang (Unprocessed Rehmannia Root), Niuxi (Twotoothed Achyranthes Root), Fabanxia (Processed Pinellia Tuber), Zexie (Oriental Waterplantain Rhizome), Mugua (Common Floweringqince Fruit) and Danshen (Danshen Root). The action of each herb is summarized in Table 1. The dosage of SQXT formula is 3 times a day, one bag (15 g per bag) at a time. Participants will dissolve the granules in hot water (100 ml), then stir and cover for 3 to 5 min, then take it orally between 30℃ to 36℃ (ante cibum).

**Table 1 Tab1:** The action of each Traditional Chinese Medicinal herb

PinYin name	English name	Latin name	Action / Pharmaceutical study
Shengshaishen	Dried fresh Ginseng	*Radix Ginseng*	1. Enhancing immune function; 2. Anti-thrombosis effect; 3. Inhibition of oxidative stress
Zhihuangqi	Astragalus membranaceus	*Radix Astragali seu Hedysari*	1. Enhancing immune function; 2. Promoting metabolic effect; 3. Lipid-lowering effect; 4. Inhibition of platelet aggregation; 5. Anti-thrombosis effect
Shanyao	Common Yam Rhizome	*Rhizoma Dioscoreae*	1. Enhancing immune function; 2. Lipid-lowering effect; 3. Glucose-lowering effect; 4. Inhibition of oxidative stress
Shengdihuang	Unprocessed Rehmannia Root	*Radix Rehmanniae Recens*	1. Bidirectional regulatory effect on immune; 2. Anti-inflammatory effect; 3. Shortening of blood clotting time; 4. Cardiovascular system protecting effect
Niuxi	Twotoothed Achyranthes Root	*Radix Achyranthis Bidentatae*	1. Enhancing immune function; 2. Anti-inflammatory effect; 3. Analgesic effect
Fabanxia	Processed Pinellia Tuber	*Rhizoma Pinelliae Preparatum*	1. Anti-atherosclerosis effect; 2. Inhibition of oxidative stress; 3. Antihypertensive effect; 4. Anti-aging effect
Zexie	Oriental Waterplantain Rhizome	*Rhizoma Alismatis*	1. Lipid-lowering effect; 2. Inhibition of oxidative stress; 3. Anti-inflammatory effect; 4. Anti-atherosclerosis effect; 5. Diuresis effect
Mugua	Common Floweringqince Fruit	*Fructus Chaenomelis*	1. Enhancing immune function; 2. Hepatoprotective effect; 3. Anti-inflammatory effect
Danshen	Danshen Root	*Radix Salviae Miltiorrhizae*	1. Inhibition of platelet aggregation; 2. Anti-atherosclerosis effect; 3. Lipid-lowering effect; 4. Inhibition of oxidative stress

Control group: Participants will take usual treatment and placebo granules. The specifications and usage of placebo are exactly the same as SQXT formula.

#### Outcome measurement

Changes of the following outcomes from baseline (week 0) to endpoint (week 12) of intervention will be evaluated.

#### Primary efficacy outcome

CIMT [39].

#### Secondary efficacy outcomes

Hyperechoic thickness of the arterial lumen wall, vascular internal diameter, PSV, EDV and Vm of bilateral carotid arteries (common carotid and internal carotid artery) and lower extremity arteries (femoral artery, anterior tibial artery, posterior tibial artery and dorsalis pedis artery), and PI, RI and S/D will be calculated according to the formula: PI = (PSV-EDV) / Vm; RI = (PSV-EDV) / PSV; S/D = PSV / EDV.FMD of the brachial artery.ABI.FPG and HbA1c.Total cholesterol (TC), triglycerides (TG), high density lipoprotein cholesterol (HDL-C) and LDL-C.TCM syndrome score [35].The indices for evaluating the quality of life are as follows: (1) The MOS 36-item short-form health survey (SF-36); (2) Quality of life scale for patients with T2DM (DMQLS); (3) Chinese version of diabetes management self-efficacy scale (C-DMSES).

#### Endpoint outcomes

The incidence of endpoint events and the time to progression to endpoint will be evaluated. Endpoints events include:The progression of peripheral artery disease is defined as bilateral carotid and lower extremity arteries stenosis or arterial occlusion.Major adverse cardiac events include cardiovascular death, non-fatal myocardial infarction, ischemic stroke, and hospitalization for heart failure.Diabetic foot ulcer.

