### Exclusion criteria

Patients with calcified plaques or unstable plaques in lower extremity or carotid arteries, arterial stenosis (vascular inner diameter stenosis ≥ 50%), or arterial occlusion.Patients who have been diagnosed with coronary heart disease by coronary angiography, or whose electrocardiogram and clinical manifestations suggest coronary heart disease, or who have had cardiovascular and cerebrovascular events, such as acute coronary syndrome and cerebral infarction.ABI ≤ 0.9.Fasting TG > 5.7 mmol/L.Patients with abnormal liver and kidney function, such as the ratio of serum alanine aminotransferase (ALT) to aspartate aminotransferase (AST) 1.5 times higher than the upper limit of normal value of that, creatinine higher than the upper limit of normal value of that, estimated GFR ≤ 60 ml·min^−1^·(1.73m^2^)^−1^.Patients with acute metabolic disorders such as diabetic ketoacidosis, or severe stress, occurred within 1 month before screening.Patients with serious illnesses whose life expectancy does not exceed 2 years, or malignant tumor, or mental diseases.Patients who are known to be allergic to the ingredients in SQXT formula or its preparations.Having a history of alcoholism or drug abuse.Women who are preparing for pregnancy, or pregnant, or lactating women.

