### Data analysis

The statistical analysis will be conducted by the third-party statistician from the Sichuan Province Evidence-based Medicine Center of TCM using Stata software (version 16.0). The statistical analysis plan is completed and confirmed before the start of trial.

The Full Analysis Set (FAS) includes participants who have been randomized to receive the drugs at least once. Missing data will be used the last observation carried forward (LOCF) method. The Per-protocol set (PPS) includes participants who follow the protocol to implement the inclusion and exclusion criteria and interventions, and complete all the visit plans. It does not include participants who drop-off, lost to follow-up, and discontinue medication for any reason. Only participant with an effective medication rate between 80 and 120% can be included in PPS analysis. The safety set (SS) includes participants who have been randomized to receive the drugs at least once and have experienced AE.

The descriptive statistics of enumeration data will be presented as frequency and percentage. Normally distributed variables will be presented as mean and standard deviation, and non-normally distributed variables will expressed by median and interquartile range. Difference between groups will be assessed with t-test, analysis of variance (ANOVA), rank sum test, and chi-square (χ2) test. Survival analysis will be used for comparison of endpoint outcome between groups, and Kaplan–Meier curve will be used to explore each possible relevant factor. The cox multiple regression model will be used to detect the influence of prognostic factors on endpoint outcome if the amount of data allows. AE will be analyzed and described in detail, and the χ2 test will be used to compare the differences between groups if necessary. The statistical significance is defined as *p* ≤ 0.05.

Subgroup analysis will be based on HbA1c. Level of HbA1c will be stratified into ≥ 8.0% and < 8.0% to evaluate correlation between glycemic control of diabetic patients with macroangiopathy and outcome indicators [37].

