## Discussion

Thickening of CIMT is an early sign of atherosclerosis and a recognized risk factor for arteriosclerotic cardiovascular disease. A systematic review and meta-analysis showed that each 0.1 mm increase in CIMT is associated with a 15% increase in the risk of coronary heart disease and a 17% increase in the risk of stroke [43]. It is recommended as an early assessment of peripheral atherosclerosis in patients with T2DM [44, 45]. Because diabetic peripheral atherosclerosis is a chronic disease, it is difficult to observe sufficient endpoint events in short-term studies. Hence, CIMT is often used as the objective surrogate indicator for primary efficacy outcome or endpoint outcome in clinical studies and systematic reviews of diabetic macrovascular complications [39, 46]. Therefore, CIMT is used as the primary efficacy outcome in this trial.

Color doppler ultrasound has unique value in the qualitative and positioning diagnosis of vascular lesions, which can evaluate the structure of arterial lumen, the nature of atherosclerotic plaque and the hemodynamics. ABI test is a good tool to evaluate the degree of stenosis and obstruction of lower extremity arteries, with high sensitivity and specificity [47, 48]. Brachial artery FMD can evaluate nitric oxide releasing function of endothelial cells to reflect the vascular endothelial function [49]. Vascular endothelial cells regulate the balance between vasodilation and contraction, anti-inflammatory and pro-inflammatory, anti-oxidation and pro-oxidation, and release vasoactive substances to maintain vascular tone and structure [50–52]. Vascular endothelial dysfunction is an early warning of cardiovascular disease [53]. Therefore, FMD test plays an important role in early recognition and effective intervention of vascular disease progression [54]. The above tests have the advantages of convenience, non-invasiveness, and repeatable measurement. They are used to objectively evaluate the changes in structure and function of peripheral arteries.

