This trial will evaluate short-term efficacy from the vascular structure and function of carotid and lower extremity arteries, glucose and lipid level, and quality of life, and long-term benefits from cardiovascular and lower extremity vascular events, and explore whether the effectiveness of the drug is related to improve inflammation, oxidative stress, and accumulation of AGEs. Moreover, lipidomics will be used to screen the biomarkers for this disease diagnosis and treatment. Lipid metabolism disorders are involved in the onset and progression of diabetes and atherosclerosis. Lipidomics provides a systematic quantitative and qualitative analysis of lipids in vivo and reveals the regulation of lipid metabolism [55]. However, the limitation of this trial is that the elderly (> 65 years) will not be included in order to exclude the influence of aging on vascular damage within a limited sample size, which leads to insufficient evidence for extrapolation of the trial results to the elderly population.

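### A 12-week trial of 114 patients cannot show long-term benefit from endpoint events, and the definition of arterial progression is ambiguous

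*Protocol article*

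**What the plan says.** Under Endpoint outcomes, the protocol article lists three kinds of event: progression of peripheral artery disease, major adverse cardiac events, and diabetic foot ulcer. It states: "The incidence of endpoint events and the time to progression to endpoint will be evaluated". The first kind is defined in one sentence: "The progression of peripheral artery disease is defined as bilateral carotid and lower extremity arteries stenosis or arterial occlusion".

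Under Data analysis: "Survival analysis will be used for comparison of endpoint outcome between groups". Kaplan–Meier curves are to be used for exploring candidate factors. Only the next step carries a condition: "The cox multiple regression model will be used to detect the influence of prognostic factors on endpoint outcome if the amount of data allows".

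The horizon is given under Outcome measurement: "Changes of the following outcomes from baseline (week 0) to endpoint (week 12) of intervention will be evaluated". The Abstract and Study design also give 12 weeks of treatment, and the text states no later follow-up. Fig. 1 is not available to this review.

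The Discussion makes two statements about events. In justifying CIMT as the primary outcome, it says that "it is difficult to observe sufficient endpoint events in short-term studies". It then says the trial will evaluate "long-term benefits from cardiovascular and lower extremity vascular events".

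**The concern.** The two Discussion statements do not fit together. The first gives scarcity of events in short studies as the reason for using a surrogate. The second assigns the same short study the task of assessing long-term benefit from those events. The eligibility rules make events rarer still: they remove patients with coronary heart disease, earlier cardiovascular or cerebrovascular events, stenosis of 50% or more, occlusion, or an ABI of 0.9 or below. The run-in then admits only patients whose glucose, blood pressure and LDL-C are at target.

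The progression definition adds a second problem. Different readings of it give different counts from the same scans, and a count that depends on the reading cannot be compared between arms with confidence.

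At stake is what a reader may conclude from an almost empty event table. The primary CIMT analysis is not affected.

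**Working it through.** **1. The plan's own figure.** The sample size rests on CIMT alone. The inputs under Sample size are means of 1.12 and 1.03 mm, SD 0.10, margin 0.03, one-sided α 0.025 and power 0.80. The effective difference is 0.09 − 0.03 = 0.06. The normal formula gives 2 × (1.96 + 0.8416)² × 0.10² / 0.06² = 43.6, so 44 per arm; the t-based version gives 45 per arm, or 90 in all (power 0.804). With 20% dropout, 45/0.8 = 56.25, so 57 per arm and 114 in all. The stated 90 and 114 reproduce. No event rate, hazard ratio or target number of events is given.

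**2. Observation time.** 114 × 12/52 = 26.3 person-years if everyone completes; 90 × 12/52 = 20.8 if only 90 are observed.

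**3. Expected events.** The annual risk *a* of any endpoint event, progression included, is an assumption. The 12-week risk is p = 1 − (1 − a)^(12/52), expected events without a treatment effect are 114p, and the chance of none is (1 − p)^114. With an assumed hazard ratio of 0.5, expected events are E = 57p + 57[1 − (1 − p)^0.5], and two-sided 5% power is about Φ(√E × ln 2 / 2 − 1.96).

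| Assumed annual risk | 12-week risk | Events, no effect | Chance of none | E at HR 0.5 | Power at HR 0.5 |
|---|---|---|---|---|---|
| 1% | 0.23% | 0.26 | 77% | 0.20 | 3.5% |
| 2% | 0.47% | 0.53 | 59% | 0.40 | 4.1% |
| 5% | 1.18% | 1.34 | 26% | 1.01 | 5.3% |
| 10% | 2.40% | 2.74 | 6% | 2.06 | 7.2% |
| 20% | 5.02% | 5.72 | 0.3% | 4.31 | 10.7% |

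The power formula is a large-sample approximation and is crude at such counts; it serves only to show the order of size. With 90 observed, events without an effect run from 0.21 to 4.5.

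**4. Events needed.** For 80% power at HR 0.5, Schoenfeld's formula gives 4 × 7.849 / (ln 2)² = 65.3, so 66. Freedman's gives (1.5/0.5)² × 7.849 = 70.6, so 71. Then 66/114 = 58% of all patients would need an event within 12 weeks. At HR 0.6 the requirement is at least 121 events, more than the number of patients.

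**5. Extreme splits.** With 57 per arm, 5 events against 0 gives a Fisher p of 0.057, and 6 against 0 gives 0.027. If an arm of 57 has no events, the exact two-sided 95% upper limit for its 12-week risk is 1 − 0.025^(1/57) = 6.3%. At a constant rate that is 1 − (1 − 0.063)^(52/12), about 24% a year. An arm without events would therefore say little.

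**6. The progression definition.**
- *Sites and sides.* The sentence can mean disease on both sides and in both territories, or disease at any site in a list. Secondary efficacy outcomes uses similar wording as a list of arteries examined. It is also unclear whether occlusion stands alone.
- *Degree.* None is given. The only cut-off is in Exclusion criteria, where "arterial stenosis (vascular inner diameter stenosis" is followed by a limit of 50% or more. Nothing links it to the endpoint.
- *New lesion.* Not required in words. If the exclusion cut-off is not carried over, a patient who enters with stenosis below 50% already meets the definition at baseline.

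**7. Timing.** Arterial outcomes are described as change from week 0 to week 12, and the 4-weekly visits under Safety outcomes mention vital signs and symptoms, not ultrasound. If arteries are scanned only at those two points, imaging progression would be found at the final scan, and its time would carry little information.

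**The case against.** The strongest reply is that the article already treats events as secondary. CIMT is primary because events are scarce, the sample size does not rest on events, and the Cox model is used only if the data allow. An article may also leave operational endpoint definitions to the full protocol or the analysis plan. Much of this stands, and it limits the point. But the condition covers the Cox model only; the survival comparison and the Kaplan–Meier curves are unconditional, and the long-term statement is in the article itself.

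Four stronger readings are tempting and are not supported:

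- *Progression requires bilateral disease in both carotid and leg arteries.* That is one reading. The parallel list under Secondary efficacy outcomes makes any listed site at least as plausible. The fault is ambiguity.
- *Patients with milder stenosis are certainly miscounted.* Exclusion criteria ties arterial stenosis to 50% or more, and the word progression suggests change. The sponsor may intend both, but the endpoint text says neither.
- *Every progression would be dated week 12, so there are no usable times.* The scan schedule is inferred, Fig. 1 could show more, and drop-outs are asked back for a last observation. Cardiac events and foot ulcers have real dates.
- *The survival analysis cannot be estimated.* At an assumed 5% a year there is a 74% chance of at least one event (100 − 26), so a log-rank test may be computable. The defect is lack of information.

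It is also fair to say that Kaplan–Meier handles censoring, which matters with 20% dropout planned. A raw percentage with a significance test would not be an improvement.

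**Conclusion.** The point holds in this limited form. On the follow-up that the text states, the trial observes at most 26.3 person-years in patients selected for absence of earlier events. Across assumed annual risks of 1% to 20%, that is about 0.3 to 6 events against the 66 to 71 needed at HR 0.5, with power of roughly 3.5% to 11%. The planned comparison is uninformative and cannot show long-term benefit; the Discussion's own remark on short studies says much the same.

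Separately, the progression definition leaves sites, degree and newness open.

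The event rates and hazard ratio are assumptions, but the conclusion does not depend on where in the range the truth lies. It does depend on there being no later follow-up, which Fig. 1 could in principle show. A reader might infer that an absence of events will be presented as benefit; the documents do not say so. Worth correcting, but no threat to the primary analysis.

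**What to change.** 1. In the Discussion, delete the statement that the trial evaluates long-term benefit from vascular events.
2. Under Data analysis, replace the between-group survival comparison by 12-week counts and cumulative incidence per arm with 95% confidence intervals, exact or allowing for censoring. A Kaplan–Meier estimate at week 12 would serve for the latter. Label these descriptive, and drop the per-factor Kaplan–Meier curves and Cox inference.
3. State how patients who drop out before week 12 are counted.
4. Under Endpoint outcomes, define progression as a new stenosis of at least 50% (the trial's own exclusion threshold) or an occlusion, absent at baseline, in any one of the carotid or leg arteries listed under Secondary efficacy outcomes.

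The cost is wording in the protocol and analysis plan. No extra scans or patients are needed. The trial gives up a between-group test of events and a claim that it cannot support.

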#### Safety outcomes

Adverse event (AE) will be collected after the participants begin to receive drugs. The record of AE includes the following: descriptive analysis, time of occurrence and termination, severity, frequency of occurrence, whether treatment is needed, and if necessary, the treatment given needs recording.

Participants will be monitored for vital signs (body temperature, respiration, heart rate, BP) during the outpatient visit every 4 weeks, and will be asked for if they have any symptoms of discomfort.

Participants will have the following tests at the beginning and end of intervention: blood, urine and stool routine examination, electrocardiogram, liver function test (ALT, AST, TBIL, AKP, GGT), and renal function test (blood urea nitrogen, creatinine). Systemic symptoms of participants will be closely observed. If a participant has suspicious symptoms of respiratory system, circulatory system, liver or kidney disease, he will be immediately tested on safety.

#### Therapeutic mechanism outcomes

Tumor necrosis factor-α (TNF-α), IL-6.Reactive oxygen species (ROS), superoxide dismutase (SOD).AGEs.Lipidomics.

### Sample size

This is a randomized, double-blind, placebo-controlled superiority trial. The primary outcome indicator, CIMT, is used as the basis for sample size estimation. The mean of CIMT of the placebo group is 1.12 mm [40–42]. In this trial, the mean of CIMT of the treatment group is estimated at 1.03 mm, and the standard deviation of two groups is 0.10. The superiority margin is 0.03 (one-sided test, α = 0.025, 1-β = 0.8). The sample allocation ratio between the two groups is 1:1. Using PASS 15 software, the minimum sample size is calculated to be 90. In addition, considering the dropout rate of 20%, we plan to enroll a total of 114 participants.

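### The sample size rests on beating a 0.03 mm CIMT margin, but the stated significance rule carries neither the margin nor the sidedness of the test

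*Protocol article*

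**What the plan says.** The Sample size section of the protocol article declares the design: "This is a randomized, double-blind, placebo-controlled superiority trial". It then gives the hypothesis parameters: "The superiority margin is 0.03 (one-sided test", α = 0.025, power 0.8). The other inputs are "The mean of CIMT of the placebo group is 1.12 mm", "the mean of CIMT of the treatment group is estimated at 1.03 mm" and "the standard deviation of two groups is 0.10". The result is a minimum of 90 participants, raised to 114 for 20% dropout.

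The Data analysis section describes the comparison in one sentence covering all outcomes: "Difference between groups will be assessed with t-test, analysis of variance (ANOVA), rank sum test" and chi-square test. The decision rule follows: "The statistical significance is defined as" p ≤ 0.05. Neither sentence gives a margin, a shifted null, a confidence-limit criterion or the number of sides. The Primary objective speaks of superiority to placebo, also without a margin. The 0.03 mm margin therefore appears once, in the sizing, and in no decision rule. The same Data analysis section says that a statistical analysis plan was completed and confirmed before the trial started; it is not available here.

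**The concern.** Superiority by a margin and superiority over zero are different claims. The first says that SQXT lowers CIMT by more than 0.03 mm relative to placebo; the second says only that it lowers CIMT. The trial is sized for the first. A reader who applies the Data analysis section literally would test the second.

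Two things are at stake. The 80% power would belong to a test other than the one carried out. And some results would count as significant although they do not establish the superiority that the sample size was built to show. Those results lie below the assumed effect of 0.09 mm, where a real but smaller benefit would fall.

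**Working it through.** **Inputs** (all from Sample size): placebo mean 1.12 mm, SQXT mean 1.03 mm, so the difference is 1.12 − 1.03 = 0.09 mm; margin 0.03 mm; SD 0.10 in both groups; one-sided α = 0.025; power 0.80; 1:1 allocation; dropout 20%.

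**Step 1: reproduce the plan's figure.** The distance from the margin is 0.09 − 0.03 = 0.06 mm.
- Normal approximation: n per arm = 2 × (1.960 + 0.842)² × 0.10² / 0.06² = 43.6, so 44 per arm, 88 in total.
- Noncentral t: power is 0.795 at 44 per arm and 0.804 at 45 per arm, so 45 per arm, **90 in total**, as stated.
- Dropout: 45 / 0.8 = 56.25, so 57 per arm, **114 in total**, as stated.

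**Step 2: is the margin needed to get 90?**

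| Hypothesis | Required size |
|---|---|
| Margin 0.03, one-sided 0.025 (t) | 90 total |
| Margin 0.03, one-sided 0.05 (normal) | 70 total |
| Margin 0.03, two-sided 0.025 (normal) | 106 total |
| No margin, two-sided 0.05 | 20 per arm (normal) or 21 per arm (t), 40 to 42 total |

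Of these, only the margin hypothesis at one-sided 0.025 gives 90. The margin is a working part of the design.

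**Step 3: smallest observed difference that passes each rule.** With SE = SD × √(2/n) and t the 97.5% point on 2n − 2 degrees of freedom, the zero-difference test passes at t × SE and the margin test at 0.03 + t × SE.

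| Per arm | SE (mm) | t × SE, null of zero (mm) | 0.03 + t × SE, margin (mm) |
|---|---|---|---|
| 45 | 0.0211 | 0.042 | 0.072 |
| 57 | 0.0187 | 0.037 | 0.067 |

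Results between the last two columns are significant on an ordinary two-sided 0.05 t-test but do not clear the margin.

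**Step 4: power at the assumed 0.09 mm.**
- 45 per arm: 0.988 for the zero-difference test, 0.804 for the margin test.
- 57 per arm: 0.997 and 0.888.

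**Step 5: dependence on the SD.** The primary outcome is change from baseline to week 12 (Abstract; Outcome measurement), and no SD of change is given. At 45 per arm, t × SE = 0.042 / 0.10 × SD, or about 0.42 × SD. Assumed SDs, for illustration:
- SD 0.05: thresholds 0.021 and 0.051 mm.
- SD 0.10: 0.042 and 0.072 mm.
- SD 0.15: 0.063 and 0.093 mm.

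The gap stays at 0.03 mm throughout.

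**The case against.** The strongest reply is that the Data analysis section never says the null is zero. It gives a generic list of tests for all outcomes, and a margin comparison of two means is itself a t-test with a shifted null. The exact null and sidedness are details that an article commonly leaves to the SAP, which is reported as confirmed before the trial started. Much of this stands: the zero null is an inference, and the SAP may already state the margin test. What remains is that the only decision rule printed here, applied as written, does not deliver the hypothesis printed under Sample size.

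Four stronger readings are tempting, and the documents do not support them:

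- **The α levels conflict, or α is doubled.** One-sided 0.025 and two-sided 0.05 agree in the favourable direction. A conflict arises only if p ≤ 0.05 is one-sided, which the article does not say.
- **The rule can be picked after seeing the data.** The SAP is reported as fixed before the start, and Blinding keeps analysts blinded until database lock, with second-level unblinding only after the analysis. An unclear article does not show an open choice.
- **The false-positive rate is 29% to 35%.** At a true difference of exactly 0.03 mm and SD 0.10, an ordinary t-test would be significant in 29% (45 per arm) or 35% (57 per arm) of trials. That is an error only against the margin null. Against the objective of being superior to placebo, those rejections are correct.
- **The sample size is wrong.** It reproduces, and it is more than enough for a zero null.

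**Conclusion.** The point holds as an inconsistency between the sized hypothesis and the stated significance rule. Read as an ordinary test of zero difference, the rule in Data analysis leaves out a 0.03 mm margin that accounts for more than half of the sample size (90 in total against about 42 without it), and the stated 80% power does not describe it.

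The 0.03 mm gap between the two success thresholds holds whatever the SD. Their location, 0.042 and 0.072 mm at 45 per arm or 0.037 and 0.067 mm at 57 per arm, assumes that the SD of 0.10 applies to the quantity analysed.

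This should be fixed. Confidence is moderate, because the SAP is not shown and may already carry the margin.

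**What to change.** In Data analysis, state the primary rule:

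- Superiority on CIMT is declared only if the lower limit of the two-sided 95% CI for the benefit (placebo minus SQXT) exceeds 0.03 mm. This is the one-sided 0.025 test against the margin.
- A CI that lies above 0 but not above 0.03 mm is reported as a difference not shown to exceed the margin.
- The p ≤ 0.05 rule is two-sided and applies to the other outcomes.

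Confirm that the SAP says the same.

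If the margin was not meant to bind, state instead that the null is zero and restate the power for that test (about 98.8% at 0.09 mm with 45 per arm and SD 0.10).

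The cost is wording only; 90 and 114 stay as they are. The downside of the binding margin is a stricter bar for success than the plain t-test, but it is the bar the sample size was calculated for.
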